### Data analysis

#### Effect evaluation and process evaluation

Quantitative methods will be used to analyze nursing practices, health service utilization, and economic outcomes. Main and secondary outcome analyses will be based on all randomized wards and selected participants. To account for within-patient correlation, due to multiple measurements from the same patient during assessment days, we will implement generalized estimating equation models with binary outcome and logic link for all rate outcome comparisons. The statistical analysis will consist of an exploration of the descriptive data of the sample, bivariate analysis with parametric and non-parametric tests, depending on the nature of the distributions (correlation, ANOVA, chi-square) and multivariate (multiple regression with independence analysis using Durbin-Watson statistics). The Cochran-Mantel-Haenszel test will be used to compare proportions. A series of exploratory analyses will be conducted on sub-groups and the impact of covariates on estimated of the effects of the intervention. A nonparametric median test will be used for HLOS comparison. In supportive analysis, HLOS will be considered as time to event data. Survival rates will be calculated and illustrated by the Kaplan-Meier method and further analyzed by the long rank test for univariate analysis. Variables that reveal prognostic or effect modifying potential on the outcome as suggested by univariate analysis will subsequently be evaluated by the proportional Cox regression for multivariate analysis. Hazard ratios with corresponding 95% confidence intervals will be reported. A *p* value of < 0.05 will be considered statistically significant. A regression model will be constructed to further explore the results obtained in the bivariate analysis, seeking to establish an explanatory model on the variables involved in improving the use of recommendations. Data will be analyzed using the program SPSS [name] Statistics version 21.

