### Randomization

Wards will be randomly allocated to the intervention or control arm using software, in blocks 1:1 with stratification by setting (medical or surgical) and hospital (to ensure homogeneity of both groups).

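### Length of stay is compared by a median test and by a supportive Cox model built through univariate screening; a pre-specified, stratum-adjusted analysis that accounts for ward would be better at little cost

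*Protocol article*

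**What the plan says.** All the rules at issue stand in the protocol article under Effect evaluation and process evaluation.

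- Comparison of stays: "A nonparametric median test will be used for HLOS comparison".
- Status of the survival analysis: "In supportive analysis, HLOS will be considered as time to event data".
- Univariate step: survival is to be "illustrated by the Kaplan-Meier method and further analyzed by the long rank test for univariate analysis".
- Selection rule: variables that look prognostic or effect-modifying "as suggested by univariate analysis will subsequently be evaluated by the proportional Cox regression". Hazard ratios with 95% confidence intervals are then to be reported.
- Significance: a p "value of < 0.05 will be considered statistically significant".
- Status of related work: "A series of exploratory analyses will be conducted on sub-groups and the impact of covariates".

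The Randomization section allocates wards in 1:1 blocks with "stratification by setting (medical or surgical) and hospital". The Setting section gives 20 wards and makes the ward the unit of analysis. The one correlation adjustment described for outcome comparisons is a generalised estimating equation for repeated measurements within patients, and it is tied to the rate outcomes.

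HLOS appears elsewhere as a mean. The secondary outcome section refers to mean stay linked to PVC bloodstream infection, and the data collection section refers to mean stay for the relevant wards. HLOS also enters the secondary hypothesis that savings will offset the cost of the intervention.

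**The concern.** Two stated choices are weaker than readily available alternatives.

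First, the supportive Cox model takes variables that look prognostic or effect-modifying in univariate tests on the same stays. Estimates and intervals for variables chosen in this way do not reflect the choosing: effects tend to be overstated and the nominal 95% coverage does not hold. The named univariate tool is also unsuited to half its task. A log-rank test on one variable tests that variable's main effect. Effect modification is a difference in the arm effect across levels of a variable, which needs an arm-by-variable interaction.

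Second, the median test reduces each stay to above or below the pooled median and discards the rest.

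Neither analysis is stated to use hospital and setting, which were known at randomisation, or to account for ward, the unit randomised. At stake are the credibility of any reported predictors or modifiers of stay, and the precision of a secondary outcome that also feeds the cost hypothesis.

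**Working it through.** The documents give no distribution, standard deviation, power target or sample size for HLOS, and no list of candidate variables. There is therefore no figure of the plan's own to reproduce on this point. The sizes below rest on stated assumptions and are shown as ranges.

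**1. False selection by screening.** Inputs: significance level 0.05 (from the plan); k independent null candidates (assumed, 5 to 20). Chance of at least one false selection = 1 − 0.95^k.

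- k = 5: 1 − 0.95^5 = 0.23
- k = 10: 1 − 0.95^10 = 0.40
- k = 20: 1 − 0.95^20 = 0.64

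The plan does not state a screening threshold. At 0.10 the corresponding values are 0.41, 0.65 and 0.88.

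These are chances of falsely selecting a variable on its main effect, which is what a log-rank screen tests. Suppose instead that modifiers were screened one at a time by interaction tests and then re-tested jointly at p < 0.05. A simulation with no true modifier (a linear model on a normal outcome as a stand-in for Cox; 800 records) gave at least one false modifier in 23–24%, 42–43% and 63–64% of runs for k = 5, 10 and 20. Screening at 0.05 or at 0.10 made almost no difference. One pre-named interaction test would give 5%.

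**2. Efficiency of the median test.** The asymptotic efficiency of the median test relative to the rank-sum test depends on the shape of the stays:

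- Log-normal stays: (2/π)/(3/π) = 0.667
- Exponential stays: (ln 2)²/0.75 = 0.480/0.75 = 0.641
- Double-exponential shape: 1/0.75 = 1.33, so here the median test is the better one

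Power where the rank-sum test has 80% at two-sided 0.05 is Φ[(1.960 + 0.842)·√efficiency − 1.960]:

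- Log-normal: Φ(2.802 × 0.816 − 1.960) = Φ(0.33) = 0.63
- Exponential: Φ(2.802 × 0.800 − 1.960) = Φ(0.28) = 0.61

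Against a log-rank test with 80% power and exponential stays, the efficiency is (ln 2)² = 0.480 and the median test has 49%.

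Simulated checks agree. Whole-day log-normal stays (log-SD 0.8, 200 per arm, independent records) gave 61% for the median test and 78% for rank-sum. With 10 against 10 normally distributed ward means, power was 51% for the median split (Fisher's exact test), 76% for rank-sum and 81% for the t test.

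**3. What data the methods need.** Kaplan-Meier, log-rank and Cox need individual stays. The secondary outcome and data collection sections describe a mean, by ward in the latter. A median test on patients and a mean by ward are different quantities, so any replacement must say which level of data it uses.

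**The case against.** The strongest reply is about weight. HLOS is secondary, the Cox work is labelled supportive, and subgroup and covariate work is labelled exploratory. A condensed article may leave the candidate list, threshold and handling of clustering to an analysis plan that is not shown. This stands as to severity, and the missing list and threshold are not held against the protocol. It does not remove the point: the median test and selection by univariate results are stated rules, and the supportive label does not make intervals after selection valid.

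Several stronger readings are tempting, and the documents do not support them:

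- *Hospital and setting enter the Cox model only if they pass the screen.* The text says that screened variables will be evaluated. It does not say that only those enter, or that the strata are left out.
- *The 40% for ten candidates is the rate of chance effect modifiers.* Under the log-rank screen as described, it counts false main-effect selections, and ten is an assumed number.
- *The hazard ratio for arm is itself unreliable.* Adding null covariates does not materially bias a randomised comparison. The harm falls on the selected variables.
- *Ward-level candidates give 94% false selection.* This carries over the intracluster correlation of 0.01 and 3821/20 ≈ 191 records per ward: design effect 1 + 190 × 0.01 = 2.90, about 25% false positives per test, 1 − 0.75^10 = 0.94. Both inputs belong to the adverse-event sample size. No intracluster correlation is given for HLOS, the number of stays per ward is unknown, and with ward means a within-ward design effect does not apply.
- *The median test always loses power.* It does so under the right-skewed shapes examined, but not under every shape.

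**Conclusion.** The concern holds for the secondary outcome HLOS. The stated rules are a median test and a supportive Cox model with variables chosen by univariate screening on the same data, and neither is stated to use the strata or to account for ward.

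The chance of at least one false selection is 23% to 64%, assuming 5 to 20 independent null candidates at p < 0.05. Power for the median test is about 61% to 63% where rank-sum has 80%, assuming log-normal or exponential individual stays. The use of a log-rank screen to find effect modifiers is wrong whatever the assumptions, because that test contains no interaction.

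The primary outcome is untouched and the Cox model is only supportive. The change is worth making, but the trial's main conclusion does not depend on it.

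**What to change.** - **Cox model (supportive).** Drop univariate selection. Fit arm, hospital and setting, plus any baseline variables named in advance, with ward-clustered standard errors suited to only 20 clusters.
- **Effect modifiers.** Name a few in advance, test each by its interaction with arm, and label the results exploratory.
- **Main HLOS comparison.** Replace the median test with a comparison stratified by hospital and setting that accounts for ward. If patient-level stays are held, as Kaplan-Meier and Cox already require, use a model for stay or log stay. If only ward means are held, use a stratified analysis of the 20 ward means. A model that yields mean stay also serves the cost hypothesis, which a median or rank test does not.
- **Consistency.** State whether HLOS is a patient-level stay or a ward mean, and align the outcome, data collection and analysis sections.

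The cost is wording, provided patient-level stays are available. If they are not, the ward-mean analysis is the feasible option, and the time-to-event analysis cannot be done as described. Adjusting ward means additively for arm, four hospital contrasts and setting leaves 20 − 7 = 13 residual degrees of freedom, which is workable but leaves little room for more covariates. The remaining downside is that covariates found important later can be reported only as exploratory.

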#### BCP environment

Firstly, an exploratory analysis will be performed of characteristics that define the behavior of each of the variables used, by means of classical descriptive techniques and the exploratory data analysis procedure. Secondly, relations will be analyzed between the professionals’ answers to the two questionnaires (EBPQ and PES-NWI), bearing in mind the sociodemographic and occupational characteristics of the sample. Differential analyses will be conducted to generate specific profiles, using general linear model analysis techniques. The individual and contextual factors reported by the respondents will be modeled, taking into account personal and occupational characteristics and the hospital ward using a multi-level analysis.

### Randomization

Wards will be randomly allocated to the intervention or control arm using software, in blocks 1:1 with stratification by setting (medical or surgical) and hospital (to ensure homogeneity of both groups).

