### Setting

The study will be conducted in five public hospitals with diverse characteristics within the Spanish National Health System, including one reference hospital and four acute care hospitals. Twenty wards will be selected and randomly allocated to either the intervention or control groups. The intervention will be delivered at ward level, and therefore, the ward will be considered the unit of analysis. Emergency, critical care, pediatric, maternity, peri-operative, operative rooms, and psychiatric areas will be excluded from the analysis, due to the fact that peripheral catheters are routinely maintained inserted for less than 24 h. Bias-compensating measures will be incorporated to homogenize nursing practice through face-to-face training in excluded wards.

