### Primary outcome measures: effect evaluation

The primary outcome will be the incidence of adverse events associated with the use of PVCs in adult inpatients. This incidence will be determined from evaluation of hospital records at 3, 6, 9, and 12 months.

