### Data collection

To mitigate control bias, each nurse manager will be provided with information to standardize catheter removal, catheter tip culture, and hemoculture extraction. Tips from all PVC removed from patients experiencing adverse events will be cultured using a semiquantitative method. Clinical, microbiological, and ward information will be collected from each patient on PVC removal.

Project investigators will collect primary and secondary outcome data using a wide range of methods, including questionnaires NWI and EBPQ to nurses, clinical audits monthly, and clinical outcome by requesting statistics report the participating wards at each hospital with the variables. Where these data are not available, clinical outcome data will be adapted from our research to collect the primary and secondary outcome data. Tools will be used for communication between facilitators, auditors, and researchers to collect at the time of activity and throughout the duration of the intervention. The mean hospital length of stay for relevant wards will be collected as reported by the hospital electronic patient management systems. This data collection system was piloted in five of the above hospital units in December 2017. Adverse events will be defined as per international guidelines for the prevention of BSIs (Healthcare Infection Control Practices Advisory Committee, USA, UK, Spain) [46–48]. Three study phases will be planned for the PREBACP study: baseline (2 months), intervention and evaluation (12 months) (Fig. 2).

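### Wards are randomised within hospital and setting, but the model stated for the rate outcomes includes neither factor

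*Protocol article*

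**What the plan says.** Protocol article, Setting: "The study will be conducted in five public hospitals with diverse characteristics within the Spanish National Health System". The same section continues: "Twenty wards will be selected and randomly allocated to either the intervention or control groups", and adds that "the ward will be considered the unit of analysis".

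Randomization: allocation is by software, "in blocks 1:1 with stratification by setting (medical or surgical) and hospital". The stated purpose is comparable groups.

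Effect evaluation and process evaluation (under Data analysis): all comparisons of rates use GEE models for a binary outcome. The only reason given is correlation between repeated measurements on the same patient. No hospital, setting or ward term is named. Covariates appear once in relation to the intervention effect: "A series of exploratory analyses will be conducted on sub-groups and the impact of covariates on estimated of the effects of the intervention". A Cochran-Mantel-Haenszel test is planned for comparing proportions, with no strata given.

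Data collection gives the study phases as "baseline (2 months), intervention and evaluation (12 months" months). On the primary outcome, the article says: "This incidence will be determined from evaluation of hospital records at 3, 6, 9, and 12 months".

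**The concern.** Five hospitals by two settings give up to 10 strata for 20 wards, about two wards per stratum if they are spread evenly. That is close to matching in pairs. Such allocation removes hospital and medical/surgical differences from the treatment comparison. The standard error shows this only if the analysis includes the same factors. If they are left out, their variation stays in the error term.

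With 10 wards per arm, between-ward variation is the main limit on power, so this is where precision can be gained without more records. At stake are power and a correctly sized test. Bias is not at issue.

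**Working it through.** **Inputs from the article (Sample size, Setting).** Control rate 44.1%; reduction 15%; two-sided alpha 0.05; power 80%; 10% missing; ICC 0.01; stated design effect 1.99; 3821 records; 20 wards.

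**The plan's own figure.** Read as a relative reduction, the target is 0.441 × 0.85 = 0.375, a difference of 0.066. The two-proportion formula (pooled variance, no continuity correction) gives 2 × 866 = 1732 records. Allowing for missing data, 1732/0.9 = 1924 or 1732 × 1.1 = 1905, both close to the stated 1920. Then 1920 × 1.99 = 3820.8, the stated 3821. An absolute 15-point drop needs only 322 records (358 with missing data) and does not reproduce the figure.

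Separately, ICC 0.01 with 200 records per ward gives 1 + 199 × 0.01 = 2.99, not 1.99. That is a different point; the calculation below works from the ICC directly.

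**Ward-level power.** Analysable records per ward: 3821/20 × 0.9 ≈ 172. Mean binomial variance: (0.441 × 0.559 + 0.375 × 0.625)/2 ≈ 0.2404. Let R² be the share of between-ward variance explained by hospital and setting. The documents do not give it, so it is assumed over a range.

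SE² = (2/10) × [0.01 × 0.2404 × (1 − R²) + 0.99 × 0.2404/172]

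At R² = 0: 0.2 × (0.002404 + 0.001384) = 0.000758, so SE = 0.0275.

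Unadjusted, the ward-level degrees of freedom (df) are 20 − 2 = 18. With four hospital terms and one setting term they are 20 − 1 − 1 − 4 − 1 = 13. Power comes from the noncentral t distribution with noncentrality 0.066/SE:

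| R² (assumed) | SE | Power, hospital + setting, 13 df |
|---|---|---|
| 0 | 0.0275 | 60% |
| 25% | 0.0252 | 68% |
| 50% | 0.0227 | 77% |
| 75% | 0.0199 | 87% |

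The unadjusted reference is 62% (SE 0.0275, 18 df). At R² = 10% the same formula gives SE 0.0266 and power of 63% on 13 df, so adjustment about breaks even there.

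**Effect on the test itself.** A simulation of 20 wards in 10 two-ward strata (20,000 runs) compared a ward-level t-test that ignores the strata with one paired within strata:

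| R² (assumed) | Type I error, ignored | Power, ignored | Power, paired |
|---|---|---|---|
| 0 | 5.1% | 62% | 57% |
| 25% | 3.6% | 63% | 64% |
| 50% | 2.1% | 64% | 73% |
| 75% | 1.0% | 66% | 84% |

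The paired test held its type I error at about 5% throughout. Full pairing leaves only 9 df, so it gains less than additive hospital and setting terms do.

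**The case against.** The strongest reply is that this argues from silence. An article commonly leaves the covariate list to a fuller document, and nowhere does it say that the main model is unadjusted. That limits how firmly the point can be put. But the article does state the model for rate outcomes, and it does say where covariates belong, namely in exploratory work. The point therefore bears on a stated choice.

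Several stronger readings are tempting, and the documents do not support them:

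- **That the strata are certainly unused.** The Cochran-Mantel-Haenszel test is stratified by construction. Its strata are unnamed, so they may be hospital and setting.
- **That a baseline event rate is held and ignored.** A 2-month baseline phase is planned, but the primary outcome is listed only at 3, 6, 9 and 12 months. The measures said to be taken before the intervention are questionnaires.
- **That the groups are exposed to chance imbalance in hospital or setting.** Stratified allocation already deals with that. Only a baseline rate would add protection, against residual differences between wards.
- **That validity is at risk.** In a ward-level analysis, leaving the strata out errs on the safe side.

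It is also fair to object that the gain is conditional. If the factors explain little, adjustment loses slightly. And the whole argument presumes that ward clustering is in the model. The article justifies its GEE by within-patient correlation only. Ignoring wards altogether would be a different fault, working in the opposite direction.

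**Conclusion.** The point holds as a mismatch between the stated design and the stated analysis, worth correcting because the correction is cheap. In a ward-level analysis, omitting hospital and setting gives a standard error that is too large and loses power once they explain more than roughly 10% of between-ward variance. Including them moves power from about 62% to 68% or 77% at assumed shares of 25% or 50%, and costs about 2 points (62% to 60%) if they explain nothing.

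These figures rest on the relative reading of the 15% reduction, ICC 0.01, 172 analysable records per ward, 10 wards per arm and a primary analysis that accounts for ward clustering. How the wards fall across the strata is not stated. No change to the stated sample size follows from this point.

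**What to change.** In the analysis section, state that the primary model accounts for clustering by ward and includes hospital and setting as fixed effects, with inference on about 13 ward-level degrees of freedom. Name hospital and setting as the strata of the Cochran-Mantel-Haenszel test. Stratifying a record-level version would not by itself account for ward clustering. Keep other covariates and sub-groups exploratory, as now.

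State whether ward adverse-event rates are recorded in the baseline phase. If they are, add the ward's baseline rate as a covariate in the same model, leaving about 12 degrees of freedom.

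The cost is a few sentences of text and about 5 ward-level degrees of freedom, or 6 with the baseline rate. No further records are needed for the hospital and setting terms.

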### Blinding

Hypothesis and variables will be blind to prevent any selection bias that might arise in the nurses participating in the data collection process. All research assistants will be blinded to group allocation. Success of blinding will be assessed at study end using the James Blinding Index. Although FIREs and intervention wards will not be blinded, control wards will be blinded. Patients will be unaware of the intervention. [name] and [name] analyze the data, all will be blinded to group allocation.

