### Secondary outcome measures: process evaluation

Nurses’ adherence to CPGs will be measured at 3, 6, 9, and 12 months with the following subcategories:1.1Multimodal intervention content will be delivered as planned (yes/no), and dosage will be delivered as often and long as planned (yes/no); face-to-face training session will be assessed by measuring the number of nurses who completed the Masterclass at the intervention phase. Feedback will be evaluated by checking the distribution of clinical audit results within intervention wards. Patient information will be assessed by monitoring the presence of informative leaflets on the ward (yes/no) and asking if the patient is aware of use of PVC and prevention recommendations for personal care. Facilitation will be measured by number of internal facilitators who completed the intervention.Clinical audits on use of PVC. Device utilization ratios will be measured by percentage of PVCs per hospital wards and number of PVC per patient. Documentation of PVC in nursing records will be assessed by percentage of fully completed records. PVC maintenance will be monitored by random, monthly clinical audits, which will document PVC size (16/18/20/22/24 gauge), site (dorsum of hand/forearm/antecubital region/upper arm), dressing integrity (clean/dry/intact), securement and time in situ (less 48 h/ between 48 and 96 h/more 96 h). Catheter tip will be measured by number of catheter tip extraction following removal of PVCs.Routine practice. Clinical effectiveness questionnaire for the prevention of PVC complications will be completed pre and post intervention. The questionnaire is made up of 35 questions in four sections, relating to general asepsis and skin antisepsis; PVC insertion, maintenance, and removal; PVC documentation; and patient and professional education.Clinical outcomes will be assessed using rates of unnecessary PVCs, rates of CRBSI, extravasation, obstruction and phlebitis, defined as per standard guidelines, and mean HLOS associated to PVC-BSIs at 3, 6, 9, and 12 months.The direct costs of implementing the multimodal intervention will be assessed using HLOS for patients and decrease rates of adverse events at 12 months (post intervention).EBCP environment:EBCP context: The contextual factors on the utilization of knowledge in clinical practice decisions and impact on hospital ward processes and practice will be assessed using the NWI tool pre-intervention. The variables are summarized into five main groups: nurses’ participation in hospital affairs; quality of nursing care; nurse management’s capacity, leadership, and support for nursing staff; size of the nursing workforce and adaptation of available human resources, and professional relation between doctors and nurses.EBCP individual: The opinions, attitudes, abilities and motivations of nurses and their links with the development of a culture of clinical practice based on the transfer of new knowledge to the healthcare given to patients will be assessed using EBPQ pre-intervention. The questionnaire is made up of 24 questions relating to professionals’ knowledge, use and attitudes towards EBCP.

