### Intervention group

The intervention will last 12 months and will be based on a theoretical model on effective knowledge mobilization, integrating a multimodal strategy related to peripheral catheters clinical practice improvement which includes the following (Fig. 1): (1) implementation of recommendations trough up-to-date protocols and posters related to hand hygiene and aseptic measures, insertion, maintenance and removal of PVC [34]; (2) use of e-learning technologies [35–37]; (3) feedback on the results and messages addressed to healthcare professionals to facilitate adherence to recommendations [38]; (4) face-to-face training sessions [39]. Masterclass related to PVC insertion, maintenance, and removal will consist of information shared about recommendation of CPGs adapted according to the needs detected by means of the questionnaire on the effectiveness of the healthcare practice; (5) leaflets with information for patients and family/careers about peripheral catheters, in appropriate language [40]; and (6) support by internal facilitators, which will be key members of staff in the organizations, to adopt best evidence based on the PARIHS theoretical model [26, 41, 42].

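### Blinding success is judged by the pooled James index alone, which can stay at or above 0.5 despite about 90% recognition of intervention wards if most control-ward answers are don't know

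*Protocol article*

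**What the plan says.** The protocol article's Blinding section says of those who assess: "All research assistants will be blinded to group allocation". The check on this is "Success of blinding will be assessed at study end using the James Blinding Index". The section gives no cut-off, no answer categories and no statement for or against results by arm. It does not say whose guesses are collected; the sentence follows directly on the one about research assistants, and I read it as applying to them.

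The same section describes unequal blinding of ward staff: "Although FIREs and intervention wards will not be blinded, control wards will be blinded". Under Intervention group, the intervention includes "up-to-date protocols and posters related to hand hygiene and aseptic measures, insertion, maintenance and removal of PVC", with patient leaflets and internal facilitators. Under Secondary outcome measures, the presence of leaflets on the ward is itself recorded. Under Control group, control wards carry on with usual practice. The visible cues are therefore on intervention wards only.

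**The concern.** The James index runs from 0 (every answer correct) through 0.5 (random guessing) to 1 (every answer *don't know*). Unblinding shows as a value below 0.5. Because the arms are pooled, many *don't know* answers in one arm can offset correct guesses in the other.

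This trial could produce that pattern. Someone who sees a poster or leaflet has a reason to name the intervention arm, whereas an ordinary-looking ward may simply draw *don't know*.

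What is at stake is how the report may describe outcome assessment. Under Definitions, phlebitis rests on pain, erythema, swelling and palpable thrombosis, and type 1 catheter infection partly on local signs. These involve judgement, so whether assessors knew the arm bears on how a difference between arms is read.

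**Working it through.** The protocol gives no blinding figure, so there is none to reproduce. The check asks what the named index returns under stated guess patterns.

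**Inputs from the protocol.** Setting: "Twenty wards will be selected and randomly allocated to either the intervention or control groups". Randomization: "in blocks 1:1 with stratification by setting (medical or surgical) and hospital". That is about 10 wards per arm, so the arms get equal weight, and 90% recognition means about 9 of 10 intervention wards.

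**Inputs assumed.** All guess patterns, and a three-way answer (intervention / control / *don't know*, abbreviated DK).

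**Formulas.**
- James = [1 + P_DK + (1 − P_DK) × K]/2, with K = (P_o − P_e)/P_e. P_DK is the pooled DK share. P_o and P_e are the observed and expected weighted shares among those who guess, with weight 0 for correct and 0.5 for wrong.
- Bang, per arm = share correct − share wrong.

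**Main example.** Intervention wards: 90% guess intervention, 0% control, 10% DK. Control wards: 10% guess intervention, 10% control, 80% DK. As shares of all answers these are 0.45, 0, 0.05 and 0.05, 0.05, 0.40.
- P_DK = 0.05 + 0.40 = 0.45, so 1 − P_DK = 0.55.
- P_o = 0.5 × (0 + 0.05)/0.55 = 0.0455.
- P_e = 0.5 × (0.05 × 0.45 + 0.50 × 0.10)/0.55² = 0.5 × 0.0725/0.3025 = 0.1198.
- K = (0.0455 − 0.1198)/0.1198 = −0.621.
- James = (1 + 0.45 − 0.55 × 0.621)/2 = 0.554.
- Bang: intervention 0.90 − 0 = 0.90; control 0.10 − 0.10 = 0.00.

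Counts of 9/0/1 and 1/1/8 in 10 wards per arm give the same 0.554.

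**Same intervention answers (90/0/10), other control answers:**

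| Control answers: intervention / control / DK (%) | James | Bang, intervention | Bang, control |
|---|---|---|---|
| 10 / 10 / 80 | 0.55 | 0.90 | 0.00 |
| 25 / 25 / 50 | 0.45 | 0.90 | 0.00 |
| 50 / 50 / 0 (chance) | 0.29 | 0.90 | 0.00 |
| 0 / 20 / 80 | 0.45 | 0.90 | 0.20 |
| 5 / 40 / 55 | 0.35 | 0.90 | 0.35 |
| 0 / 90 / 10 | 0.10 | 0.90 | 0.90 |

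**Where it crosses 0.5.** With even guesses among control answers that are not DK, James is 0.486 at 60% control DK and 0.520 at 70%. If all those guesses are right, no guess in either arm is wrong, so K = −1 and James reduces to P_DK. It then reaches 0.50 only when control DK is 90%: (0.10 + 0.90)/2.

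**Two further patterns.**
- Intervention answers 80% right, 5% wrong, 15% DK, with control at 10/10/80: James 0.61, Bang 0.75 and 0.00.
- In each arm 40% guess, all correctly, and 60% answer DK: James = P_DK = 0.60, Bang 0.40 in each arm. The weight given to DK can thus also hide unblinding present in both arms.

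**The case against.** The strongest case against is that the masking needs a particular set of answers, and nothing in the protocol points to it. Allocation is 1:1 within strata that include hospital, and leaflet presence is recorded. An assistant who recognises intervention wards by their materials could well infer control where the materials are absent, and the James index detects that. Over a 5-point grid of all control-arm patterns, with 90% of intervention wards recognised, the index is at or above 0.5 in only 29 to 33%. This stands, and it limits the point to a possibility.

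A reader might infer that the index would report acceptable blinding whenever about 90% of intervention wards are recognised. The documents do not support that: the result depends on the control-ward answers, and without a stated threshold the protocol does not say what value would count as success.

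It is also fair that the James index is established, that results by arm are not excluded and could appear in an analysis plan not shown, and that the primary outcome is taken from hospital records, where ward posters need not be visible. These arguments keep the point small. They do not remove it, because the article does fix one pooled index as the means of judging success.

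**Conclusion.** The point holds as a minor improvement. Used alone, the James index can sit at or above 0.5 (0.55 in the main example) while about 90% of intervention wards are recognised, provided control-ward answers are mostly *don't know*: somewhere between 60% and 70% if the remaining guesses are even, 90% if they are all right. It falls below 0.5 if control wards are guessed at chance (0.29) or are recognised as well (0.10 to 0.35).

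This rests on assumed guess patterns, a three-way answer, and 0.5 as the reference because it is the random-guess value. It would go too far to say that the protocol's index certifies failed blinding, or that only one-sided unblinding escapes it. The check is a study-end diagnostic, so no primary estimate, test or sample size is affected.

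**What to change.** Replace the sentence on the James index with, for example: *Guesses of allocation (intervention / control / don't know) will be collected at study end. The James index will be reported together with the Bang index, calculated separately for intervention and control wards with confidence intervals. Success of blinding will not be concluded from the pooled index alone. If the intervention-arm index indicates unblinding, this will be stated wherever outcome assessment is described.*

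The two arm values should be read together. If 90% in both arms guess intervention and 10% guess control, Bang is +0.80 and −0.80 and James is 0.50; the guesses then do not distinguish the arms.

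The cost is one sentence. Both indices use the same guesses, so no further data are needed. The only downside is that the statement on blinding may turn out less favourable.
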